### Trial Status

This is the first version of the protocol. The first pre-screened participant was invited to be informed about the study on May 27^th^, 2021. The recruitment phase or the data collection phase of the trial will be completed by the end of March 2022 including post-test and post-test 2 measurements.

### Statistical analysis plan

Statistical Models will be conceptualized and set up within the structural equation modeling and the mixed-effects modeling frameworks and estimated with corresponding packages from the statistical analysis software R. Each hypothesis will be tested for statistical significance using α = .05.

#### Effects of mental training interventions on pre-post changes in variables of interest

In order to evaluate intervention-related effects on variables of interest, a mixed-effects modeling approach will be applied. Effects of time of assessment (pre-test/post-test for primary outcome variables and pre-training session/post-training session for secondary outcome variables respectively) and intervention group (socio-emotional mental training/mindfulness-based mental training/waitlist control group), as well as the interaction between time and group will be defined as fixed effects. Dummy coding with the waitlist control group as reference will be used for the intervention group variable. Additionally, we will control for participant-related random effects.

In addition, latent change scores for each primary outcome variable respectively will be computed with two timepoints (pre-test/post-test). The change in outcomes will be modeled as a latent variable and this latent change will be predicted by the treatment condition (path c in Fig 6). A correlation between the latent change score and initial levels on the primary outcome variable of interest is evaluated.

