Participants will have to meet the following inclusion criteria: between 18- and 65-years age, resident of Berlin, and proficiency in German language.Participants will be excluded if they do not have access to internet or the necessary technical equipment, if they have an educational background in psychology, if they have regular spiritual practice (including yoga practice with meditative component), if they take medication that influences physiological markers or if they take psychiatric medication, if they have participated in stress reduction programs previously, if they suffer from chronic illness or pain, or if they have a history of or current psychiatric diagnosis. Further, participants will be excluded based on the cut-off scores for the following questionnaires: Toronto Alexithymia Scale-20 (TAS-20; [189, 190]); exclude if score greater than 60), Patient Health Questionnaire-9 (PHQ-9; [190]); exclude if scores greater than 19), and Generalized Anxiety Disorder-7 (GAD-7; [191]); exclude if scores greater than 15). Participants endorsing suicidality on the PHQ-9 will also be excluded.In a third step, individuals who meet all the inclusion and exclusion criteria will be randomly assigned to one of three groups. Initially, the three groups will be oversampled, to ideally form *n* = 200 per group.In the next step all these individuals will be invited to take part in online informational webinars about the study. These online events will serve the purpose of providing interested individuals with information about mindfulness meditation and concepts underlying the socio-emotional mental training. Further, information about exact dates and study procedures will be given. After this event, individuals will have to indicate their interest in participating in the study.In case, the number of interested individuals is higher than the targeted *n* = 100 per group, then the extra number of interested individuals will be excluded based upon study-relevant considerations to make sure that we have three comparable final groups with *n* = 100 each. The participants will then complete the written informed consent indicating their consent to participate in the study.Next, individuals who provide informed consent to take part in the study will undergo screening phone calls with licensed mindfulness-based meditation instructors. In these individual calls, participants will undergo mental health screening using the Standardized Assessment of Severity of Personality Disorder-Abbreviated Scale [192] and the Composite International Diagnostic-Screener [193]. These screening calls would further allow us to exclude individuals who are evaluated as meeting criteria for clinical diagnoses or psychological instability as identified by the meditation instructors, using the screening instruments. This is an important step as the current study is a first step towards exploring the effects of low-intensity online socio-emotional interventions in a non-clinical population. In future studies, this line of research may be extended to clinical populations.astly, if based on the above-mentioned individual screening calls with meditation teachers some individuals have to still be excluded from the study, then the above sampling procedure will be repeated in order to fill any participant gaps in each group.

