
An estimated 300 individuals, 100 per intervention group, will be recruited. A priori effect size and power calculations have been performed based on the results from the previous mental training study, the ReSource project [67], which developed and validated the interventions being applied in the current study. Power analyses were conducted using G*Power [194] for analysis of variance with repeated measurements and interactions between group and intra-group variables. The analyses elements were as follows: an alpha level of .05, with a power (1-ß) of .80, 3 groups and 2 measurement occasions, a correlation of variables with repeated measurements of .39 which is the lower limit of retest reliability for the Cortisol Awakening Response (CAR; [195]), and an assumed small effect size of *f* = .10. This results in a total sample size of *n* = 297. For the additional third measurement time (post-test 2 following socio-emotional intervention given to waitlist control group) power analysis was conducted in a similar manner as above.

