#### Phase 1 measures

Data on various measures of trait and state vulnerability, resilience, and social cohesion will also be obtained from the recently completed first phase of the CovSocial project (osf.io/jvb98). The data will be used to test hypotheses that predict impact of phase 1 trait and longitudinal assessments on intervention-related change in phase 2.

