#### Background, context and socio-demographic variables

Where necessary, we will account for socio-demographic variables (such as age, gender, marital status, number of children, education in years, and household income) and other context variables including COVID-19 related questions (e.g., access to green spaces, job status, covid-related health status, living situation, financial and job risk factors etc.) assessed in the context of the extensive assessment in phase 1. Predictive value of relevant context- and demographic variables on differences in variables of interest at pretest and their training-related change will be explored similarly to the prediction by latent trait factors assessed in phase 1. Besides, initial levels on outcome variables of interest at pretest will be controlled for by including autoregressive paths in respective models.

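### The efficacy models leave out the pre-screening PHQ-9, GAD-7 and TAS-20 scores, a small and nearly free gain in precision for BDI-II, STAI and TAS-20

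*Protocol article*

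**What the plan says.** All references are to the protocol article.

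- *Effects of mental training interventions on pre-post changes in variables of interest*: the mixed model has time and group, "as well as the interaction between time and group will be defined as fixed effects", plus participant random effects. A parallel model predicts the latent change in each primary outcome from treatment, with change and initial level allowed to correlate. No prognostic score is named in either.
- *Sample and sampling procedure*: PHQ-9, GAD-7 and TAS-20 are scored at pre-screening and serve as exclusion cut-offs, for example "Patient Health Questionnaire-9 (PHQ-9; [190]); exclude if scores greater than 19". Random assignment follows among those who qualify. *Procedure* places disclosure of the arm at the later webinar, and the pre-test after that.
- *Phase 1 measures*: "The data will be used to test hypotheses that predict impact of phase 1 trait and longitudinal assessments". The prediction section of the analysis plan regresses pre-test values and latent change on Phase 1 factors, and the Introduction calls this exploratory.
- *Background, context and socio-demographic variables*: "Where necessary, we will account for socio-demographic variables" and context variables from Phase 1. Pre-test outcome levels are controlled through autoregressive paths in the models concerned.

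**The concern.** Three symptom and trait scores exist for every participant before randomisation, complete by construction because eligibility depends on them. Two measure nearly the same construct as a later outcome (PHQ-9 and BDI-II; GAD-7 and STAI), and the third is the outcome scale itself, since TAS-20 is repeated at pre- and post-test. One pre-test reading is a noisy measure of a person's level. A second, earlier reading can remove some of that noise from the comparison between arms.

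The scores also have a modest advantage over the pre-test. In this unblinded trial the pre-test is taken after participants know their arm. The screening scores cannot have been affected by that knowledge.

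What is at stake is precision on these self-report outcomes. The only covariate provision beyond the pre-test level is the conditional one for socio-demographic and context variables, which fixes no list and does not mention the screening scores.

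**Working it through.** **Inputs from the article** (*Sample and sampling procedure*). Test level .05, target power .80, three arms, two occasions and f = .10. For the pre-post correlation the article borrows a figure from the cortisol awakening response (CAR): "a correlation of variables with repeated measurements of .39 which is the lower limit of retest reliability". The stated total is 297, with 300 planned. The test level in the analysis plan agrees: "Each hypothesis will be tested for statistical significance using α = .05".

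**Step 1. The stated sample size.** For the group-by-time interaction, λ = f²·N·m/(1 − ρ), with 2 and N − 3 degrees of freedom.

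- N = 297: λ = 0.01 × 297 × 2 / 0.61 = 9.738; power .8002.
- N = 296: power .7987.

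So 297 reproduces exactly, from a model without covariates.

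**Step 2. Power for the self-report outcomes.** The value .39 belongs to CAR. Assume instead pre-post correlations of .5 to .7 for questionnaires, with the same f and N = 300, before dropout:

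| ρ | λ | power at 300 | N for 80% |
|---|---|---|---|
| .5 | 6/0.5 = 12 | .880 | 244 |
| .6 | 6/0.4 = 15 | .942 | 196 |
| .7 | 6/0.3 = 20 | .984 | 148 |

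**Step 3. Gain in the time-by-group mixed model.** With complete data, a covariate that is constant over time and enters as a main effect is orthogonal to the within-person contrast. A simulated data set with 100 per arm gave a standard error for time-by-group of 0.1518 with and without it.

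With a covariate-by-time term, the share of change variance explained is (c_post − c_pre)² / [2(1 − r)]. Here r is the pre-post correlation, c_pre and c_post are the score's correlations with pre-test and post-test, and equal variances are assumed. This share is zero when c_pre = c_post. Over assumed ranges r = .5 to .7, c_post = .40 to .55 and c_pre = .4 to .6, the largest value is (.40 − .60)² / 0.6 = 6.7%.

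**Step 4. Gain in the baseline-adjusted model.** The treatment coefficient is the same whether post-test or change is regressed on treatment and pre-test. One added score lowers the residual variance by

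(c_post − r·c_pre)² / [(1 − r²)(1 − c_pre²)].

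Over the same assumed ranges:

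- Best corner (r = .5, c_post = .55, c_pre = .4): (.55 − .20)² / (.75 × .84) = .1225/.63 = 19.4%.
- Centre (.6, .5, .5): (.50 − .30)² / (.64 × .75) = .04/.48 = 8.3%.
- Unfavourable corner (.7, .40, .6): (.40 − .42)² / (.51 × .64) = .0004/.3264 = 0.1%.
- Exactly zero where c_post = r·c_pre.

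On a grid in steps of .01, the middle 80% of combinations lies between 1.8% and 13.1%.

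**Step 5. What that buys.** A 2% fall makes 300 participants act like 300/.98 = 306. A 13% fall gives 300/.87 = 345, and a 19% fall gives 300/.81 = 370. The standard error shrinks by about 1%, 7% and 10% (1 − √.98, 1 − √.87, 1 − √.81).

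**The case against.** **A journal article need not list covariates.** A fuller plan or the separate preregistration may name them, and nothing in the article is false. This is why the point is only a minor suggestion. It does not fall altogether, because the article writes out the efficacy model and makes its other covariates conditional on an unstated need.

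**The gain is assumed.** No correlation between a screening score and an outcome is given. Excluding PHQ-9 above 19, GAD-7 above 15, TAS-20 above 60 and anyone with a psychiatric diagnosis narrows the scores and tends to lower their correlations. This stands, and it argues for the lower part of the range.

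**A reader might infer that the trial has no power to spare and needs this adjustment.** The documents do not support that. The tight figure of 297 against 300 rests on the CAR correlation, and the adjustment does nothing for CAR. At the correlations assumed for self-report outcomes, power before dropout is already .88 to .98.

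**A reader might also infer that Phase 1 data go unused, or that any Phase 1 factor would serve as a covariate.** Neither holds. Phase 1 factors are already planned as predictors of pre-test level and change, as a deliberate exploratory aim. They are broad factors for vulnerability, resilience and social cohesion, and nothing shown establishes one as a match for the stress, loneliness or resilience scales. Only the first three, retrospective waves are a condition of invitation. A rule based on each person's last completed wave would therefore mix different times and kinds of rating.

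**Conclusion.** The point holds as a missed efficiency of minor weight. The efficacy models do not include the screening PHQ-9, GAD-7 and TAS-20 scores, although these are held for everyone from before randomisation. In a baseline-adjusted model the matching score would lower residual variance by roughly 0 to 19%, and by about 2 to 13% in most combinations tried. That rests on assumed correlations of .5 to .7 (pre-post), .40 to .55 (score with post-test) and .4 to .6 (score with pre-test). Range restriction makes the lower part more likely.

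The benefit is confined to BDI-II, STAI and TAS-20. In the time-by-group mixed model it is nil for a main effect and at most about 7% for a covariate-by-time term. Leaving the scores out does not bias the training effect, and the stated sample size does not depend on including them.

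**What to change.** - State that, for the three outcomes below, the treatment contrast comes from the baseline-adjusted form: latent change, or post-test, regressed on treatment and the pre-test level.
- In that model enter one fixed covariate per outcome: PHQ-9 for BDI-II, GAD-7 for STAI, and the screening TAS-20 for TAS-20. Fix the list before outcome data are analysed.
- Do not rely on a main effect of the score, or on a score-by-time term without baseline adjustment, in the time-by-group mixed model.
- Add a Phase 1 factor score only where the same construct was measured at one of the first three waves, and use the same wave for everyone.
- Leave the power statement as it is, and claim no gain for CAR.

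The cost is a few lines of analysis-plan text and one degree of freedom per model. No new data, visits or participants are needed.

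### The training effect on each primary outcome has two analyses, neither named as deciding, and it is unclear whether either adjusts for pre-test; adjusting would raise power from about 77% to 90% at the planning values

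*Protocol article*

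**What the plan says.** All of this is in the Protocol article.

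- **Statistical analysis plan, opening paragraph:** "Each hypothesis will be tested for statistical significance using α = .05".
- **Effects of mental training interventions on pre-post changes in variables of interest:** first, a mixed model with fixed effects of time, group and time by group, waitlist as reference, and participant random effects. Pre-test is one of the two responses, not a covariate. Then: "In addition, latent change scores for each primary outcome variable respectively will be computed with two timepoints (pre-test/post-test"), with the latent change predicted by condition as path c of Fig 6. On baseline: "A correlation between the latent change score and initial levels on the primary outcome variable of interest is evaluated".
- **Background, context and socio-demographic variables:** "initial levels on outcome variables of interest at pretest will be controlled for by including autoregressive paths in respective models". The models are not listed.
- **Mediation analysis:** path c returns as the effect without the mediator, to be compared with c'.
- **Sample and sampling procedure:** "Power analyses were conducted using G*Power [194] for analysis of variance with repeated measurements and interactions between group and intra-group variables". The test is at α = .05 with 80% power, for three arms each measured twice. The pre-post association is taken as "a correlation of variables with repeated measurements of .39 which is the lower limit of retest reliability", here of a cortisol measure, and the effect as "an assumed small effect size of *f* = .10". The resulting total is 297.

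No sentence calls either efficacy analysis primary, confirmatory, supportive or a sensitivity analysis, and none says what happens if they differ.

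**The concern.** With two occasions and complete pairs, the mixed-model interaction with a free group effect at pre-test is the difference in mean change between arms, unadjusted for the starting level. Path c can be that same quantity, or it can be the group effect at a given pre-test value, depending on which baseline statement governs it. The text does not settle this.

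Two things are at stake. If path c is unadjusted, the plan measures a pre-test on everyone and then leaves its precision unused in every efficacy test. If path c is adjusted, one outcome and one contrast have two different tests at .05, and the plan does not say which is the trial's answer.

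Any pre-test difference between arms moves the two estimates apart. Such differences may exceed chance here. Random assignment comes before the webinar, the statement of interest and consent; the webinar introduces the assigned training (Procedure); and surplus volunteers are excluded on loosely described grounds (Sample and sampling procedure).

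**Working it through.** **Inputs.** From Sample and sampling procedure: α = .05, power .80, k = 3 groups, m = 2 occasions, ρ = .39, f = .10, n = 100 per arm. Assumed: two-sided contrasts, unit SD, complete pairs, and ρ = .6 and .8 to show a range.

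**1. The plan's own figure.** For the within-between interaction, λ = f²·N·m/(1 − ρ), with df 2 and N − 3. At N = 297, λ = .01 × 297 × 2/.61 = 9.74 and power is .8002; at N = 296 it is .7987. The stated 297 reproduces, and it is computed for the unadjusted interaction.

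**2. From f to a contrast.** If both trainings shift post-test by d and waitlist by 0, the change means (0, d, d) have SD d·√(2/9), and half of that is the interaction effect: f = d·√(2/9)/2. So d = .20/√(2/9) = 0.424.

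**3. Same or different estimator?** In one simulated data set (100 per arm, ρ = .39, true shift 0.30), first training arm versus waitlist:

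| Analysis | Estimate | SE | p |
|---|---|---|---|
| Mixed-model time by group | 0.306 | 0.149 | .040 |
| Change on group | 0.306 | 0.149 | .041 |
| Change on group and pre-test | 0.426 | 0.127 | .001 |

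The first two coincide; conditioning on pre-test gives another estimator.

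**4. Power of one contrast at d = 0.424, ρ = .39.**
- Unadjusted: residual variance 2(1 − ρ) = 1.22; SE = √(1.22 × 2/100) = 0.156; 0.424/0.156 = 2.72; power about 77%.
- Adjusted: residual variance 1 − ρ² = 0.848; SE = √(0.848 × 2/100) = 0.130; 0.424/0.130 = 3.26; power about 90%.

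**5. How often the verdicts differ.** The two statistics correlate √((1 + ρ)/2) = √.695 = .83. From 20,000 simulated three-arm trials per setting:

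| ρ | Power, unadjusted / adjusted | Verdicts disagree, d = 0.424 | Either significant, no effect |
|---|---|---|---|
| .39 | 77% / 90% | 15.1% | 7.7% |
| .6 (assumed) | 91% / 96% | 5.9% | 7.1% |
| .8 (assumed) | 99.7% / 99.8% | 0.2% | 6.3% |

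A bivariate-normal calculation at ρ = .39 agrees: 15.3% disagreement and 7.6% under no effect. For the 2-df group test at ρ = .39, power is 81% versus 93%, disagreement 13.9%, and either significant under no effect 7.4%.

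**The case against.** **The efficacy section alone does not describe two different tests.** That is right. With change only correlated with initial level, and group free to relate to pre-test, step 3 shows the same result twice. The statement on autoregressive paths sits in the section on background variables, directly after a sentence about exploring predictors, and may concern those models only. A two-occasion latent change score also contains a pre-to-post path fixed at 1, so the term does not by itself prove adjustment. Fig 6, which lays out path c, is not visible here. A reader might infer that the plan certainly contains conflicting tests, so that an outcome can be both significant and non-significant. The documents do not support that without the condition that path c is pre-test-adjusted.

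**The mixed model looks like the main test.** It comes first, it matches the power calculation, and path c goes on to serve the mediation work. This is a reasonable inference, but the text never states it, and path c is introduced under efficacy. If it is correct, the main test is the less precise one.

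**The size can be overstated.** At d = 0.3 disagreement would be 22%, with power of 48% versus 63%, but that is not the planned effect when both trainings work equally. It becomes relevant only if the arms differ: with one arm midway between waitlist and the other, f = .10 gives that arm about 0.245 SD and about 21% disagreement. Moreover, .39 is a lower limit for one cortisol measure, so other outcomes may show smaller gaps. The 7.5% is an error rate only if whichever test is significant gets reported, and the plan states no such rule.

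**Labels may stand elsewhere.** The article points to a preregistration and supplementary protocol files, not shown. They could name the deciding test; the two baseline statements in the article would still need reconciling.

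**Conclusion.** The point holds in a conditional form. The plan gives two analyses of one training effect per primary outcome, ranks neither, and handles baseline in two ways that it does not connect. On one reading the tests coincide and both give up about 13 percentage points of power (77% against 90%) that the collected pre-test would supply. On the other they are different estimators, whose verdicts disagree in about 15% of trials at the planned effect, with at least one significant in about 7.5% when there is no effect. The lost precision is then confined to the mixed model.

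These sizes assume ρ = .39, 100 complete pairs per arm, two-sided .05 and equally effective trainings. They become small at high correlations. This is a worthwhile correction of the analysis wording, not a fault that invalidates the design.

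**What to change.** In the section on pre-post changes, state that each pre-post efficacy hypothesis is decided by the group effect adjusted for pre-test: regress post-test, or latent change, on group and pre-test. Do not force a common pre-test mean across arms, because selection after randomisation means that equality cannot be taken for granted. Label the unadjusted time-by-group interaction a sensitivity analysis. Use path c in the mediation model as the total effect, with the same pre-test adjustment. Replace the correlation statement and the unnamed models in the background section by one baseline rule that lists the models it covers.

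The cost is a sentence or two and no new data. The second model can no longer support a claim on its own. The sample size of 297, computed for the unadjusted interaction, becomes conservative: at ρ = .39 the adjusted residual variance is 0.848/1.22 = .695 of the unadjusted one.
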